### Analyses

Statistical analysis will be undertaken by an investigator masked to group allocation (LS). Primary analysis will use the intention to treat principle, using the last observation carried forward for participants who withdraw before the end of the trial. Baseline data from each outcome measure for each treatment group will be reported using descriptive statistics. Continuous data will be compared between groups by fitting a regression model using generalized estimating equations [93] to baseline, 10 and 26 week measurements with an interaction term between the intervention group and a three-level factor indicating time of measurement. The generalized estimating equation model will assume a Gaussian family, identity link, and unstructured working correlation matrix for repeated measurements on participants. Conventional variance estimates will be used. Where continuous data exhibit skewness not overcome by transformation, non-parametric methods (Mann–Whitney U) will be used for simple comparisons. Statistical significance will be at p < 0.05 and analyses will be performed using STATA 11.

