## Background

Cerebral palsy (CP) is the most common cause of physical disability in childhood with an incidence of 2.11 per 1000 live births [1]. It describes a “group of permanent disorders of the development of movement and posture, causing activity limitations that are attributed to non-progressive disturbances that occurred in the developing fetal or infant brain” [2]. In 2013, the Australian Cerebral Palsy Register reported that 71% of children with CP achieved ambulation and 91% were classified with spasticity as the predominant motor type. Children with lower limb spasticity often experience a range of impairments including weakness, tightness, reduced motor control and muscle selectivity. These impairments can lead to limitations in functional ability, balance, ambulation and fitness compared to typically developing peers [3,4]. Physiotherapy intervention focuses on reducing these impairments and optimising functional, goal-related performance.

Focal, intramuscular Botulinum Toxin-Type A (BoNT-A) injections to the lower limb are commonly used in combination with physiotherapy as the temporary reduction in spasticity provides an opportunity to facilitate rehabilitation outcomes [5-8]. For ambulant children with CP (Gross Motor Functional Classification System, GMFCS-E&R, Levels I-III [9]), there is strong evidence that injections of BoNT-A are safe and reduce muscle tone in spastic, active and non-fibrotic lower limb muscles for approximately 12–16 weeks [6,7,10-12]. BoNT-A impacts body structure and function, however the accompanying physiotherapy often targets activity level outcomes (International Classification of Functioning, Disability and Health, ICF [13]).

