### Recruitment

#### Sample size

According to CONSORT guidelines, the sample size calculation is based on adequate power for comparison between the functional effects of group-based and individual physiotherapy intervention at 10 weeks (T2, immediately post intervention). A change score difference of two or more points between groups on the performance scale of the COPM (primary outcome measure) would be considered clinically meaningful [56]. A previous study of lower limb intramuscular injections of BoNT-A yielded a standard deviation of changes of 1.4 and 1.7 for COPM performance [17]. Based on a mean change of two points on the COPM performance scale and a standard deviation of 1.6 points for both groups, significance (alpha) level of 0.05 and 80% power, we require 24 participants (12 in each group). Allowing for 20% drop out, a total of 30 participants (15 in each group) will be recruited.

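### Last observation carried forward in the primary analysis gives children lost before T2 zero change, which shrinks or shifts the T2 difference by an amount set by who leaves and when

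*Protocol article*

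**What the plan says.** The Analyses section sets the missing-data rule for the primary intention-to-treat analysis: "using the last observation carried forward for participants who withdraw before the end of the trial". The section names no other missing-data method. The comparison is made by "fitting a regression model using generalized estimating equations" to the three visits with a group-by-time interaction, a Gaussian family and an "unstructured working correlation matrix for repeated measurements on participants". It adds: "Conventional variance estimates will be used".

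Outcome measures and procedures places T1 in the two weeks before injection, T2 at 10–12 weeks on completion of the rehabilitation block, and T3 at 26 weeks to assess retention. There is no assessment between T1 and T2.

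The Sample size section powers the trial at T2: "Based on a mean change of two points on the COPM performance scale and a standard deviation of 1.6 points for both groups", which gives 12 per arm. It then states: "Allowing for 20% drop out, a total of 30 participants (15 in each group) will be recruited".

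**The concern.** A child who leaves before T2 has only the pre-injection value to carry forward, so the rule records no change at T2 or T3. Every child is due to receive BoNT-A, and the plan expects improvement. Loss before T2 is also what the withdrawal criteria mainly describe: too few therapy hours, or complications that require leaving the rehabilitation pathway.

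A child who leaves after T2 has the 10-week value used at 26 weeks. That assumes the retention which T3 exists to measure. The Background says injections "reduce muscle tone in spastic, active and non-fibrotic lower limb muscles for approximately 12–16 weeks", so T2 comes before or at the start of the period in which tone reduction ends, and T3 comes after it.

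The model then treats the filled-in values as observed. At stake are the size of the T2 difference, the power that the 20% allowance was meant to protect and, if the arms lose children unequally, the type I error.

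**Working it through.** **Inputs from the protocol.** Difference 2 points; SD of change 1.6 in both arms (the source study gave a "standard deviation of changes of 1.4 and 1.7 for COPM performance"); alpha 0.05; 80% power; 12 per arm evaluable; 15 per arm recruited; 20% drop-out.

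**Assumed, not in the protocol.** Two-sided test; mean change in the individual arm of 0 to 3 points; timing and split of drop-out; drop-out unrelated to outcome; within-child correlation 0.5 in the repeated-measures runs.

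**1. The plan's own figure.** For a two-sample t-test, the noncentrality is 2 / (1.6 × √(2/n)). At n = 11 it is 2.93 and power is 79.6%. At n = 12 it is 3.06 and power is 83.3%. So 12 per arm is right, and 24 / 0.8 = 30.

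**2. Expected T2 difference under carry-forward.** With d children per arm of 15 lost before T2, and mean changes m_G (group) and m_I (individual):

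E(difference) = m_G × (1 − d_G/15) − m_I × (1 − d_I/15)

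With equal loss d, this is (1 − d/15) × 2.0:
- d = 1: 1.87
- d = 2: 1.73
- d = 3 (the planned 20%): 0.8 × 2.0 = 1.6

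**3. Power at T2, 3 of 15 lost per arm before T2** (100,000 simulated trials per row, t-test on change):

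| Mean change, individual v group | Carry-forward, 15 + 15 | Observed, 12 + 12 |
|---|---|---|
| 0 v 2 | 81% | 83% |
| 1 v 3 | 74% | 83% |
| 2 v 4 | 62% | 83% |
| 3 v 5 | 46% | 83% |

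Power falls as mean change rises because zeros mixed with larger changes widen the spread within each arm. At 2 v 4 the average sample variances are about 2.7 and 4.8, against 1.6² = 2.56.

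With fewer losses, still at 2 v 4:
- 1 lost per arm: 84% against 89%
- 2 lost per arm: 74% against 86%

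A three-visit Gaussian model with unstructured correlation and model-based variance (400 simulated trials, mean change 2 v 4, 3 lost per arm) gives 62% with carry-forward and 86% on available data.

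**4. No true difference, unequal loss before T2.** With a common mean change of 2, the shift is 2 × (d_I − d_G)/15. The t-test results are:

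| Lost, group v individual | Shift | Type I error, carry-forward |
|---|---|---|
| 3 v 3 | 0 | 2% |
| 2 v 4 | 2 × 2/15 = 0.27 | 4% |
| 1 v 5 | 2 × 4/15 = 0.53 | about 12% |

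Observed data give 5% throughout. For 1 v 5 the three-visit model gives 16% with carry-forward and 7% on available data.

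**5. T3, loss after T2 only** (three-visit model, 400 simulated trials):
- 3 + 3 lost, difference constant at 2: power 93% with carry-forward, 91% on available data. No loss of power.
- 3 + 3 lost, difference falling from 2 to 1: expected estimate 0.8 × 1 + 0.2 × 2 = 1.2 (simulated 1.16), against 0.98 on available data. Power is 45% against 37%.
- No true difference, 1 v 5 lost, common change fading from 2 to 0.5: expected shift 1.5 × (1 − 5)/15 = −0.40 (simulated −0.41), against −0.02 on available data.

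**The case against.** Four points can fairly be made for the plan.

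- **The power figures rest on assumed inputs.** The protocol gives a difference and an SD, but not the mean change in each arm or when the 20% leave. With an individual-arm change near zero, carry-forward costs only about two percentage points. With one early loss per arm at 2 v 4 it costs about five. This stands, and it is why a range is shown.
- **Unequal loss is not established.** Entry requires commitment to six weekly sessions in either format, session length and frequency are the same in both arms, and group venues are to be mutually convenient. The 1 v 5 split has no source, and a 2 v 4 split does not raise type I error above 5%. This stands too. The 0.27-point shift at 2 v 4 remains.
- **Both arms receive toxin.** A reader might infer that the rule freezes a peak toxin effect and so inflates the retention result at T3. The protocol does not support that. It says how long tone is reduced, not that COPM or gait scores peak at T2. A fade common to both arms cancels from the between-group contrast when loss is equal.
- **Removing the imputation does not by itself secure validity under missing at random.** The planned model is a GEE, which is not a likelihood method and in general needs stronger missingness assumptions. This stands and alters the remedy. The observed-data power figures likewise assume drop-out unrelated to outcome, and withdrawals for complications or poor attendance may not meet that.

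None of this supports carry-forward as the primary rule. Its error depends on who leaves and when, and the planned model can be fitted to incomplete visits without it.

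**Conclusion.** The point holds at T2 and, with conditions, at T3. It concerns a method the protocol fixes, not a detail left for a fuller document.

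- **T2, equal loss before T2:** the difference shrinks in proportion to the loss, to 1.6 at the planned 20%. That is below the two points named in H1. The power cost runs from about 2 to 37 percentage points over assumed individual-arm changes of 0 to 3.
- **T2, unequal loss:** the difference moves towards the arm that keeps more children when both arms improve equally. Type I error rises above 5% only for strongly unequal splits.
- **T3:** the between-group contrast is biased, in either direction, only if loss is unequal or the difference changes after T2. Equal loss after T2 does not reduce power.

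It would go too far to say that the rule always loses power, that it always creates a false difference when drop-out is unequal, or that it necessarily inflates the T3 comparison.

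**What to change.** Delete the carry-forward rule from the primary analysis. Analyse all observed T1, T2 and T3 values of every randomised child in the allocated arm, without imputation.

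Preferably replace the GEE with a likelihood-based linear mixed model with group, time and their interaction and an unstructured covariance over the three visits. This is valid under missing at random. If the GEE is kept on available data, state the stronger missingness assumption that it generally needs. Keep carry-forward at most as a labelled sensitivity analysis.

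The cost is a short rewrite of the Analyses paragraph, including the change of model. No extra children, visits or data are needed, and N stays 30.

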#### Exclusion criteria

Children will be excluded from the study if they:

1. Are unable to complete baseline assessments;

2. Have had orthopaedic or neurological surgery and/or other new spasticity management (e.g. Baclofen) within six months prior to commencing the study;

3. Have intellectual or behavioural difficulties which would limit their ability to participate in the assessment or therapy protocols;

4. Have medical co-morbidities which prevent them from exercising safely (e.g. cardiac or respiratory instability, uncontrolled seizures).

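### The group-by-time model with baseline as an outcome gives differences in mean change; adjusting for baseline would usually be more precise and would handle chance imbalance better

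*Protocol article*

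**What the plan says.** The Analyses section specifies the model for continuous outcomes closely. It is a GEE fitted "to baseline, 10 and 26 week measurements", "with an interaction term between the intervention group and a three-level factor indicating time of measurement". It will "assume a Gaussian family, identity link, and unstructured working correlation matrix for repeated measurements on participants", and "Conventional variance estimates will be used". Withdrawals are completed "using the last observation carried forward for participants who withdraw before the end of the trial".

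Baseline is therefore one of the three modelled responses. The only other use of it in that section is descriptive: "Baseline data from each outcome measure for each treatment group will be reported using descriptive statistics". Neither a baseline covariate nor a common baseline mean is mentioned. Every child should have a baseline value, because children are excluded if they "Are unable to complete baseline assessments".

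The Sample size section works on the change scale throughout. The target is a two-point difference in COPM performance change, and the SD of 1.6 is taken from a previous study that "yielded a standard deviation of changes of 1.4 and 1.7 for COPM performance".

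**The concern.** Allocation is random, so the two arms have the same expected baseline mean. A model with a free arm difference at T1 spends information estimating a quantity known to be zero in expectation. The follow-up effect then becomes a change-score contrast, in which the slope on baseline is fixed at 1 rather than estimated.

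Two things follow when the true slope is below 1:

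- **Precision.** The change score carries more baseline noise than it needs to, which matters in a trial of 24 to 30 children.
- **Imbalance.** If one arm happens to start lower, part of its later gain is regression to the mean, and the change-score contrast credits that to treatment. The Randomisation section makes chance imbalance plausible. Children are recruited in blocks of four to eight up to 30, which is about 4 to 8 recruitment periods (30/8 = 3.75; 30/4 = 7.5). With two geographical clusters in each, only about 8 to 16 clusters are allocated.

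**Working it through.** **1. The plan's own figure.** Inputs from the Sample size section: difference 2, SD of change 1.6 in both arms, alpha 0.05 (taken as two-sided), power 80%. The standard error at 12 per arm is 1.6 × √(2/12) = 0.653, so the noncentrality is 2/0.653 = 3.06 on 22 df. The t-based power is 83.3% at 12 per arm and 79.6% at 11, so 12 per arm is reproduced. With 20% dropout, 24/0.8 = 30. The sizing is correct for a change-score analysis.

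**2. What the stated model estimates.** Two arms by three times gives six cell means, and group, time and interaction terms give six parameters, so the mean model is saturated. With complete data the fitted means are the observed means. The T2 interaction term is then the difference between arms in (T2 mean minus T1 mean), and likewise for T3.

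The stated GEE was fitted to one simulated data set with 12 per arm and no true arm difference. The interaction estimates were 0.8363 (T2) and 0.2541 (T3), identical to the raw differences in mean change, and the free baseline difference was −0.497. Requiring equal baseline means moved the T2 estimate to 0.640 and reduced its model-based standard error from 0.564 to 0.501. This is one illustrative data set, not an estimate of the typical gain.

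**3. Large-sample precision.** Assume equal variance s² at baseline and T2, with correlation r. Per child:

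- change score: variance 2s²(1 − r)
- baseline-adjusted: variance s²(1 − r²)
- ratio: (1 + r)/2

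**4. Small-sample cost of estimating the slope.** With 12 per arm and normal data, estimating the slope multiplies the adjusted variance by 1 + 1/(22 − 2) = 1.05, where 22 is the within-arm degrees of freedom. The ratio becomes 1.05 × (1 + r)/2. Power comes from simulating the covariate analysis (21 df) with the SD of change held at 1.6.

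| assumed r | (1 + r)/2 | with slope cost | power, change score | power, adjusted |
|---|---|---|---|---|
| 0.3 | 0.65 | 0.68 | 83% | 94% |
| 0.5 | 0.75 | 0.79 | 83% | 91% |
| 0.7 | 0.85 | 0.89 | 83% | 87% |
| 0.9 | 0.95 | 1.00 | 83% | 83% |

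Simulated variance ratios agree with the third column to within about 0.01. In terms of sample size, the gain is worth about 47%, 27%, 12% and 0% more children (1/0.6825 = 1.47; 1/0.7875 = 1.27; 1/0.8925 = 1.12; 1/0.9975 = 1.00).

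**5. Imbalance.** Given an observed baseline difference d, the change-score estimate is shifted on average by −(1 − r)d under equal variances. Take r = 0.5 as an example. The baseline SD implied by a change SD of 1.6 is 1.6/√(2 × 0.5) = 1.6, so one standard error of the baseline difference at 12 per arm is 0.653. An imbalance of that size shifts the estimate by 0.5 × 0.653 = 0.33 COPM points, against a target of 2.

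**The case against.** The strongest defence is that nothing here is wrong or inconsistent. The hypotheses are framed as improvement, the target is a change-score difference, the SD is an SD of change, and the model delivers that contrast. It is a common and valid repeated-measures analysis. All of that stands.

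A reader might go further than the document allows in five ways:

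- **That the baseline is wasted.** It is used, by subtraction. What is lost is only the gap between a slope of 1 and the best slope.
- **That the estimate is biased.** Over randomisations it is unbiased. The shift in step 5 is conditional on the imbalance actually observed.
- **That the trial is underpowered because of this choice.** It is not: 12 per arm reproduces on the plan's own inputs.
- **That the gain is certainly large and free.** The document gives no correlation between baseline and follow-up. It quotes a COPM retest ICC of 0.76 to 0.89. That is reliability, not correlation across ten weeks that include treatment, but it gives no ground for excluding r above 0.7. At r = 0.9 the cost of the slope cancels the gain.
- **That adjustment makes up for the clustered allocation.** The figures treat children as independent, and no calculation here supports such an offset.

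The article also does not write out the main effects. The free T1 difference is inferred from the usual way such a model is fitted. That inference is reasonable, since the section specifies family, link, working correlation and variance estimator yet names no baseline constraint.

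**Conclusion.** The point holds as an avoidable loss of precision and a weaker handling of chance imbalance, not as an error that invalidates the analysis. On the usual reading of the model, the T2 and T3 effects are differences in mean change. Baseline adjustment would cut the variance by roughly a third at r = 0.3, a fifth at r = 0.5, a tenth at r = 0.7 and nothing at r = 0.9.

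These sizes rest on an assumed r, equal variances at baseline and follow-up, complete data, 12 independent children per arm, and the plan's difference of 2 and change SD of 1.6. They are worked for COPM performance at T2. The same reasoning applies to the other continuous outcomes and to T3, but the gain there depends on correlations the document does not give.

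**What to change.** State one of the following in the Analyses section before allocation is unmasked, because the choice moves the estimate:

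- keep all three time points as outcomes but constrain the T1 means to be equal across arms, by omitting the group main effect and retaining the group-by-T2 and group-by-T3 terms; or
- model T2 and T3 only, with the child's baseline value of the same outcome as a covariate.

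The cost is a change of wording and about one degree of freedom. No new data are needed and the sample size can stand. The two-point target keeps its meaning, because under randomisation the adjusted difference estimates the same effect as the difference in change. The geographical cluster allocation needs separate treatment, and the power figures above do not cover any further model terms added for it.

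### Model-based GEE variances with one dispersion for three visits cannot be relied on to give a 5% test in about 30 children; the size and direction of the error depend on visit SDs that the protocol does not give

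*Protocol article*

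**What the plan says.** The Analyses section compares the arms on continuous outcomes by "fitting a regression model using generalized estimating equations [93] to baseline, 10 and 26 week measurements", with a group-by-time interaction over three time points. The model "will assume a Gaussian family, identity link, and unstructured working correlation matrix for repeated measurements on participants". The next sentence reads "Conventional variance estimates will be used". Significance is set at p < 0.05 and STATA 11 is named. No reference distribution, small-sample correction or visit-specific variance is mentioned. Withdrawals are handled by carrying the last observation forward under intention to treat.

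The Sample size section gives the scale of the trial: "we require 24 participants (12 in each group"), and then "Allowing for 20% drop out, a total of 30 participants (15 in each group) will be recruited". The same model serves both primary outcomes, COPM and EVGS, at T2 and T3.

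**The concern.** A Gaussian GEE with a working correlation matrix (not a covariance matrix) has one scale parameter. The unstructured option frees the three correlations but leaves one variance common to all visits. Model-based variances take that working model as true. If the spread differs between visits, the standard error of a change contrast borrows from a visit that is not part of the contrast.

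The documents give no grounds for assuming equal spread. COPM is a bounded 1 to 10 rating of activities chosen because they are a problem, scored before and after treatment. T3 lies at 26 weeks, beyond the 12 to 16 weeks of reduced tone cited in the Background and after usual therapy may resume. GMFM-88, which is also continuous, has reported floor and ceiling effects.

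At stake is whether p < 0.05 and the matching confidence intervals for the main comparisons mean what they say. If the standard error is too small, one format may be declared better by chance too often. If it is too large, power is lost.

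**Working it through.** **The plan's own figure.** Inputs from the Sample size section: difference 2 points, SD 1.6 in both arms, alpha 0.05 (two-sided assumed), power 80%. The normal formula gives 2 × 1.6² × (1.960 + 0.842)² / 2² = 10.05, so 11 per arm. With the t distribution, power is 79.6% at 11 per arm and 83.3% at 12. So 12 per arm is right, and 24 / 0.8 = 30. The sample size reproduces and is not in question.

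**Which n applies.** Last observation carried forward gives every child three values, so the planned analysis has about 30 children (15 per arm). The 24 is the number required before the dropout allowance.

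**Formula.** With complete data and a saturated group-by-time mean, the GEE estimate for T2 is the difference in mean change. Write σ1², σ2², σ3² for the visit variances, c for the T1–T2 covariance, n for the number per arm and φ = (σ1² + σ2² + σ3²)/3.

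- True variance: (2/n)(σ1² + σ2² − 2c).
- Model-based variance: (2/n)(2φ − 2c).

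They agree when 2φ = σ1² + σ2², that is when σ3² = (σ1² + σ2²)/2. Equal SDs satisfy this but are not the only case that does.

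**Worked example, large samples.** Assume SDs 1.6/1.6/1.2 and correlation 0.5. Then φ = (2.56 + 2.56 + 1.44)/3 = 2.187 and c = 0.5 × 1.6 × 1.6 = 1.28. The model uses 2 × (2.187 − 1.28) = 1.813; the true value is 2.56 + 2.56 − 2.56 = 2.56. The SE ratio is √(1.813/2.56) = 0.842. A z test then rejects with probability P(|Z| > 1.96 × 0.842) = 9.9%. More children would not remove this part.

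**Reference distribution and divisor, equal SDs.** P(|t28| > 1.96) = 6.0% for 30 children; P(|t22| > 1.96) = 6.3% for 24. If the scale also divides by the number of observations rather than that number less the six mean parameters, the critical value shrinks by √(28/30) or √(22/24), giving 6.9% and 7.4%.

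**Simulation.** Null trials, normal data, independent children, complete data, T2 contrast, z test. The table is for 15 per arm and correlation 0.5, with 200,000 trials per row (Monte Carlo standard error below 0.1 point). Every SD is an assumption except that 1.6 at each visit with correlation 0.5 gives an SD of change of √(2.56 + 2.56 − 2.56) = 1.6, the planning value. In the column heads, N and N−p are the two scale divisors. Pooled means that the correlation is scaled by the common dispersion; by visit means that it is scaled by each visit's own variance.

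| SD at T1/T2/T3 | Pooled, N | Pooled, N−p | By visit, N | By visit, N−p |
|---|---|---|---|---|
| 1.6/1.6/1.6 | 7.1% | 6.2% | 6.9% | 6.1% |
| 1.5/1.7/1.7 | 6.1% | 5.2% | 6.6% | 5.7% |
| 1.7/1.5/1.5 | 8.5% | 7.5% | 7.6% | 6.7% |
| 1.2/1.8/1.8 | 4.3% | 3.7% | 6.4% | 5.6% |
| 2.0/1.4/1.4 | 11.0% | 9.9% | 9.6% | 8.5% |
| 1.6/1.6/1.2 | 13.4% | 12.3% | 9.1% | 8.1% |
| 1.2/1.6/2.0 | 2.1% | 1.7% | 4.2% | 3.6% |

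A further run of the 1.6/1.6/1.2 row gave 13.9% in the first column. With 12 per arm and equal SDs, the results lie between about 6% and 8%. One trial can err both ways: SDs 1.2/2.0/1.6 gave 6.4% to 9.0% at T2 and 1.8% to 4.2% at T3, across the four variants.

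**Alternatives.** A t test on change with its own variance and 28 degrees of freedom stayed at about 5% in every row. Uncorrected robust variances with a z test gave about 7% in every row.

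**The case against.** The strongest reply is that much of the excess does not come from the quoted sentence. With equal SDs, plain robust variances do no better than conventional ones, and under the N−p divisor the conventional standard error is almost unbiased. What remains is the z reference and, under the other divisor, the scale. The plan states neither, and an analysis plan might settle both. The larger figures need SDs that the documents do not give, and they shrink if the software scales the correlation by visit variances: the 1.6/1.6/1.2 row falls from 13.4% to 9.1%. For EVGS the documents offer no particular reason to expect unequal spread.

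All of this stands as a limit on size. It does not remove the point. The single dispersion follows from the model that the protocol does fix, and its effect persists under either divisor, under either scaling and in large samples.

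A reader might go further and infer that the intervals and p-values for both primary outcomes are wrong. The documents do not support that: in some unequal-SD cases the errors cancel to about 5%. Nor do they support the inference that conventional rather than robust variance is the whole fault. Allocation by geographical cluster is a separate issue and is not counted here.

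**Conclusion.** The point holds in conditional form. The stated model can give standard errors that are too small or too large, in a direction not known in advance, and with the usual z test it does not reliably hold 5%. At the planned size of about 15 per arm, the error rate is about 6% to 7% with equal visit SDs, mostly from the reference distribution and the divisor. Small SD differences give about 5% to 8%. The assumed larger differences give about 2% to 14%, and those extremes depend on the chosen SDs and on how the software scales the correlation. These figures rest on a two-sided z test, complete normal data, independent children and correlations of 0.3 to 0.5. The effect of carried-forward values on the visit spread was not modelled. This is a correctable weakness of inference, not a fatal flaw.

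**What to change.** Replace the GEE and the sentence on variance estimates with a REML linear mixed model. Keep the same group-by-time means, use an unstructured residual covariance (a separate variance at each visit), and base tests and intervals on small-sample t degrees of freedom such as Kenward–Roger. If GEE is kept, use robust variances with a small-sample bias correction and a t reference; plain robust variances are not enough. If the named software version lacks these options, a t-based comparison of change at each visit held 5% in the check above.

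The cost is a few lines of analysis text and no new data. Where visit SDs are equal, the t reference widens intervals by 2.048/1.960, about 4.5%, and a divisor correction adds up to √(30/28), about 3.5%. Where the present method overstates the variance, intervals become narrower. The sample size is unchanged, since 12 per arm already gives 83.3% power under a t test.
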